## Abstract

**Background:**

In this study, the focus is on how to support the competence development needed for nursing assistants in home care. Home care services for older persons can be challenging concerning the nature of the interpersonal interaction and communication needed to care for and respond to the diverse needs of older people who seek to live well in our communities. This implies a need to offer more person-centred care (PCC) to older persons. However, there is a lack of knowledge on how to develop such competence. We, therefore, developed A Person-centred CommunicaTION (ACTION) programme, which is a web-based educational intervention aimed at supporting competence development for nursing assistants. The research objective is to evaluate the ACTION programme with respect to participants’ responses to and the effect of the intervention.

**Methods:**

A multicentre case–control study with pre- and post-assessments was designed. The ACTION programme will be implemented at home care units, in two different geographic areas in Sweden. A total of 300 nursing assistants will be recruited: 150 for the intervention group and 150 for the control group. We will evaluate the impact measures and the process. Pre- and post-assessments will be performed with data collected via a) audio recordings of communication, b) a questionnaire on self-efficacy communication skills, PCC, empathy and job satisfaction, c) user data, evaluation forms, field notes and observations, and d) interviews. The data will be analysed with descriptive and analytic statistics and/or qualitative methods for meanings.

**Discussion:**

This study has the potential to contribute to the evidence supporting competence development required to offer person-centred and quality home care to older persons and to meet upcoming needs for flexible and easily accessible competence development.

**Trial registration:**

ISRCTN64890826. Registered 10 January 2022, https://www.isrctn.com/ISRCTN64890826

## Background

This study protocol presents the implementation of A Person-centred CommunicaTION (ACTION) programme targeting nursing assistants (NAs). NAs must have the competence needed to care for and respond to the diverse needs of older people who seek to live well in their communities. Home care services are a part of Sweden’s welfare system, delivering health and care services at home, and supporting older persons to remain living in their homes for as long as possible. Home care services are foremost delivered by NAs, who are one of the largest occupational groups in Sweden [1]. They have a prominent position, performing most patient/client-direct care to older persons at home. The workload and work complexity have increased for NAs, and the Swedish welfare system is facing challenges in keeping competent staff for the care of older persons and in supporting good working conditions [1, 2]. The recruitment and retention of competent staff with the skills needed for quality care for older persons is a future challenge. Therefore, we developed the ACTION programme to support competence development in home care for older persons.

### Current challenges related to individualised care and the significance of person-centred communication skills

The home care of older persons is multifaceted and can be challenging concerning the nature of interpersonal interaction and communication needed to succeed with care actions and to support older persons’ dignity and well-being. Home care is important for supporting healthy ageing for older persons living at home and needs to build on communication and interaction that shows respect and dignity while acknowledging individual needs. The research suggests that communication and person-centred care (PCC) are particularly helpful to uphold dignity, empathy, well-being, and humanity in the care of older persons [3–5]. The communication and interaction between older persons and NAs are important for a successful outcome of individualised care [6]. A positive relationship with time for individual concerns is supportive and can demonstrate trust and empathy. These factors also affect an individual’s self-management of illness [7] and thereby health and well-being.

Considering the interpersonal nature of individualised care, the communication skills of staff become a key competence. While communication occurs naturally during nursing activities, research suggests that everyday conversations can be used to elicit information, normalise unpleasant procedures and manage interactions and relationships [8]. However, communication and interaction are subjected to challenges due to older persons’ fragility, existential concerns, and emotional needs, which are commonly vaguely expressed and difficult to notice [4, 8, 9]. To successfully manage various caring situations, the competence of individual NAs is crucial. Thus, skills in person-centred communication are vital for the individualised care of older persons with diverse needs and circumstances. Feasible interventions with better utilisation of competence are required.

### Work complexity and challenges related to key competences of NAs

The work complexity of home care of older persons can result in challenging situations for NAs related to communication and ethical or existential concerns [4, 8–10]. There might also be difficulties in organisational structures [4, 10], for instance, strict rules, time limits and regulations of home care visits. Moreover, changes in the welfare system related to rationalisation and marketing make NAs’ work more standardised and detailed, leading to less ability to control their daily work [11]. In contrast, research indicates that PCC can have a positive impact on job satisfaction [12]. In addition, improving communication skills among staff can also benefit both patient and staff outcomes [3].

There are approximately 135 000 NAs in municipality home care or nursing homes in Sweden [1]. Most of them have vocational training from high school health education and a majority are women (91%). The number of employees without training or formal college or university education is estimated to be lower than those with training. A relatively large proportion of employees in municipal care are reported to be low qualified, and some staff lacks sufficient competency to ensure that older persons receive the care they require [13, 14]. In the near future, before 2028, over 35 000 NAs will reach retirement age [1]. Hence, there are challenges in ensuring the right competence of staff in the municipal care of older persons.

Competence is a complex concept defined as a combination of skills, knowledge, attitudes and abilities [15]. Competence development in this area requires a pedagogical approach integrating education with personal experiences and abilities. Educational support is needed for NAs to meet the individual needs of older persons [16].

### Previous implementation of person-centred care or communication interventions

Currently, PCC is implemented in a variety of healthcare contexts [5]. There is an ongoing study with a focus on the effect of education on PCC for nursing staff in nursing homes [17]. However, there is no previous study with a focus on person-centred *communication* tailored to home care, even though there have been some communication intervention studies in other healthcare settings [3, 18–21]. Previous studies on implementing person-centred and empathic communication in home care are scarce. In addition, interventions in home care are complex, not least related to the work complexity and challenges in sustaining competent staff needed for individualised quality care of older persons. More research is necessary on how to successfully implement and evaluate educational interventions with suitable approaches and components for NAs in home care. Therefore, we developed the ACTION programme for competence development targeting NAs in home care. The research objective is to evaluate the full-scale implementation of the ACTION programme with respect to participants’ responses to and the effect of the intervention.

### Theoretical frameworks of the ACTION programme

#### Development of the educational intervention

The ACTION programme was developed to address the challenges of keeping and safeguarding competencies imperative for quality home care services and to meet current and upcoming needs for flexible and easily accessible education. A participatory-driven design for co-creation, involving NAs, managers, and researchers, was used. The programme combines the essential competences of PCC and communication for the development of NAs’ expertise, needed for high-quality person-centred care and the well-being of older persons. ACTION is a short, mainly web-based education with a clear focus on the practical implementation of person-centred communication, influenced by previous research in this field and from the researchers’ previous studies in the COMHOME project [22]. Different pedagogical approaches are used to support the practical use of this knowledge when caring for older persons in their homes. The intervention is designed to be flexible, accessible, and easy to implement. The programme was developed based on four core components: I) knowledge of key competence in communication and person-centred care, II) self-directed and reflective learning, III) flexibility and accessibility, and IV) efforts to stimulate and encourage participant activity [23].

The ACTION programme was first evaluated in a small-scale feasibility study [23]. The evaluation of the small-scale intervention showed promising results. The findings emphasise the benefits of a web-based learning format and the critical importance of organisational support and available resources. A relatively high level of participation by NAs was observed. This might indicate that the education was found to be meaningful. The web-based format was easy to use, and the NAs appreciated the flexibility and accessibility. After this small-scale feasibility study, some refining work has been made based on the findings.

#### Implementation strategy

The implementation strategy is tailored to attributes known to be important and to allow the intervention to fit local circumstances. Facilitation is considered important, and we involved NAs and managers to obtain suggestions and feedback. To achieve the best possible outcomes, with respect to participation and acceptance, the implementation work is guided by Everett Rogers [24] in combination with the work by Boaz et al. [25]. The guiding principles and strategic attributes for successful implementation are to provide a relative advantage compared to other strategies (e.g., traditional classroom education); compatibility with home care practice and work organisation; and to minimise the complexity (i.e., easy to understand and access). This is combined with a flexible and web-based approach [25] by using a web-based learning platform designed for education. To ensure accessibility, the research team will provide support and different solutions to allow participants access either through computers at their workplace, tablets provided by researchers, or the participants' mobile phones. Facilitators will support their participation, together with weekly e-mail reminders and newsletters. We are aware of differences in technical skills among the participants. The learning platform is widely used by students in higher education in Sweden, is considered easy to use, and requires a limited amount of IT experience. The researchers will ease any technical problems and support the NA’s access. Close collaboration between researchers and individuals within the home care units will be prioritised and is considered imperative for implementation.

#### Theoretical framework for person-centred communication

Our approach to person-centred communication builds on a combination of theories on PCC and communication. The theoretical point of departure for PCC is the theory and philosophy of psychologist Carl Rogers [26]. Carl Rogers emphasises a caring approach based on principles and values of acceptance, caring, empathy, and sensitivity in human interactions [26]. PCC and communication are intricately linked and widely recognised as important concepts in quality of care. The literature on PCC describes communication, respect, autonomy, empathy, and empowerment as fundamental components [27–29]. PCC reflects humanistic values of respect for the person and individual rights to self-determination, with mutual respect and understanding [30]. The ability to be sensitive and listen is essential, which includes the acknowledgement and confirmation of emotions [31]. The communication of care providers is an important competence to facilitate PCC, and PCC can be accomplished and supported by communication competencies. There are, however, challenges in achieving PCC in reality.

In addition to the framework of PCC, the basis for communication is built on the theory by Watzlawick et al. [32] and partly on the model for empathic communication by Suchman et al. [33]. Communication and interaction between people have two main functions: exchanging information and building relationships. Communication is a complex process and is defined as the act of transmitting meanings and messages between people. Everything one does is a message: actions, words and silences all have a message [32]. Emphatic communication can be understood as sequences of interactions with emphatic opportunities. A basic skill for being empathic is to recognise patients’ expressions of emotional concerns, even if not explicitly expressed, to invite further exploration while acknowledging the emotions and making the patients feel confirmed and understood [33]. Recognising emphatic opportunities can help improve empathic responses with an impact on care quality and satisfaction for patients and staff.

#### Pedagogical strategies

The ACTION programme has a blended learning approach, combining e-learning and face-to-face instructions [34]. Our pedagogical strategies aim to support a self-directed and reflective learning approach. By using flexible and experience-based learning, the goal is to stimulate and encourage NAs to learn and mature in their person-centred communication skills. This is in line with Knowles's [35] theory of adult learning, highlighting the importance of a self-directed learning approach with reflection. To develop knowledge and mature in one’s understanding, previous work experiences can be a resource for learning. The pedagogical strategies are adopted in the ACTION programme, and the education is structured into six stepwise modules, combining important components of PCC and communication, please see Fig. 1. These modules contain a combination of web-based lectures, quizzes, reflection assignments and one on-site group supervision. The theoretical content includes knowledge on, for example, careful listening, asking questions, being attentive and empathic, and verbal and nonverbal communication.

**Fig. 1 Fig1:**
[figure not shown]
Overview of the stepwise education modules during the six educational weeks (W1-W6)

## Methods

### Design

The ACTION programme is designed as a multicentre case–control study with a pre-post, intervention design. Previous research has stressed a need for further controlled studies to examine the tendency observed in individual studies [3]. Implementing interventions, such as the ACTION programme in home care, is complex as several components can interact and affect each other. Therefore, our research is guided by the framework for complex interventions [36], combined with a multifaceted implementation strategy [25]. Both implementation outcomes and intervention outcomes will be evaluated [36], and the STROBE guidelines for the conduct and dissemination of observational studies will be used [37].

Qualitative and quantitative measures will be combined, and multiple data from audio-recorded real-time communication, questionnaires and interviews will be collected and analysed. The settings and samples for the project are home care units located in western and mid-Sweden, in both urban and rural areas. The intervention will be conducted during the regular work of the NAs and will not affect the regular care. For an overview of the intervention and data collection, please see Fig. 2.

**Fig. 2 Fig2:**
[figure not shown]
Overview of the intervention and data collection

The ACTION programme is a collaboration between the University of Borås and Mälardalen University, but is initiated by the University of Borås, who also is primarily responsible for the study.

### Settings and samples

Approximately 300 NAs will be recruited for the study. Participants will be randomly assigned to either control (*n* = 150) or intervention group (*n* = 150). The recruitment will be organised into two stages: the first stage will be performed by researchers at University 1 with the recruitment of 75 participants in each group, e.g., intervention versus control group. In the next stage, researchers at University 2 will repeat the procedure with the recruitment of 75 participants in each of the intervention and control groups. The power calculation estimated that a sample size of 115 NAs was needed in each group to capture a statistically significant difference in outcomes after the intervention, calculated with a rate ratio of 1.5 with 80% power and a Type I error rate of 5%. The estimation of the sample size is based on the hypothesis that NAs in the intervention group will have a greater number of empathic responses after intervention than those in the control group. To account for dropouts, this number was extended to 150 NAs in each group.

Home care units will be recruited based on contacts with managers who are willing to implement the educational programme for NAs at their unit. A researcher from the project will visit the home care units and provide information about the ACTION programme to the NAs. Every NA, at each home care unit, will be offered to participate in the ACTION programme. After informed consent, they will be included. All participating home care units will be blinded, and do not know if their unit will be part of a control or an intervention group. The randomisation is done by recruiting every second unit to the intervention versus the control group, to aim for an even distribution of the number of units in each group. The intervention groups will be offered the education during implementation, and the control groups will be offered the education after completion of all data collection to compensate for their effort to collect data as controls.

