### Analyses and data processing

Data will be analysed with quantitative and/or qualitative methods. Descriptive statistics will be used for participants’ characteristics to present findings of the coding of empathic opportunities, reports on self-efficacy communication skills and job satisfaction, and data on participants' adherence.

For analysis of our primary outcome, we will compare the number of empathic statements and the number of responses to an empathic opportunity with a continuer rather than a terminator, similar to the study by Tulsky et al. [51]. The number will be calculated in pre- and post-assessments and compared between the control and intervention groups. Considerations will be made regarding hierarchical and clustered data, e.g., both the NAs and older persons may be recorded several times. For the analysis of differences between the intervention and control groups, we will consider using a generalised linear model form of regression analysis. For statistical analysis of differences between subgroups, chi-square tests will be used for responses given on nominal scales and independent t-tests or corresponding nonparametric tests if needed for responses given on continuous scales.

For analysis of secondary outcomes, all self-reported measures from the survey will be treated as continuous variables and compared between the intervention and control groups. Descriptive statistics will be used to analyse the answers reported. We will consider subgroup analysis with inferential statistics on differences related to sex, age, and native language. The analysis will follow the same statistical analysis as described above for the primary outcome. All statistical analyses will be two-sided and performed in IBM SPSS Statistics software Version 25.

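### The 80% power with 115 nursing assistants per group takes no account of allocation by home care unit, so the design does not deliver the stated power

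*Protocol article*

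**What the plan says.** All the relevant statements on sample size and allocation are in the protocol article, Methods, Settings and samples.

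- **Sample size.** The article says "a sample size of 115 NAs was needed in each group", "calculated with a rate ratio of 1.5 with 80% power and a Type I error rate of 5" per cent. The hypothesis behind it is that "NAs in the intervention group will have a greater number of empathic responses after intervention than those in the control group".
- **Inflation.** "To account for dropouts, this number was extended to 150 NAs in each group". No other increase is mentioned.
- **Allocation.** "The randomisation is done by recruiting every second unit to the intervention versus the control group". Every NA at a participating unit is invited, units are not told which group they will be in, and the stated aim is an even number of units per group. An earlier sentence speaks of randomly assigning participants, but the only mechanism described works by unit.
- **Analysis.** Under Analyses and data processing, "All statistical analyses will be two-sided". The same section promises that hierarchical and clustered data will be considered. Its example is repeated recordings of NAs and older persons; the home care unit is not named.

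**The concern.** The calculation counts NAs, while the design allocates units. NAs in one unit work under the same manager and routines and may visit the same clients. In the intervention arm they also share local facilitators and the group supervision session. Their counts are therefore likely to be positively correlated, and 115 NAs carry less information about the group difference than 115 independent NAs would.

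The 35 additional NAs per group do not cover this, because the article has already assigned them to dropout. An analysis that correctly respects the units will show the lost power and cannot restore it.

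At stake is how the primary comparison is read. If the result is not significant, a stated power of 80% invites the conclusion that a 1.5-fold effect has been made unlikely, when the study could reliably detect only a larger one.

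**Working it through.** **Inputs from the article.** 115 evaluable NAs per group; rate ratio 1.5; power 80%; Type I error 5%, two-sided; 150 recruited per group.

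**Inputs assumed, because the article gives none.** Units per arm, unit size (taken as equal) and ICC.

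**1. The plan's own figure.** For a Poisson count compared on the log rate ratio,

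n = (1.960 + 0.842)² × (1/λ₀ + 1/(1.5 λ₀)) / (ln 1.5)².

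The control rate λ₀ is not stated, so 115 cannot be reproduced uniquely. A rate of 0.5 per recording gives 160 per group, 0.70 gives 114 and 1.0 gives 80. The figure of 115 is matched by a rate of about 0.69 with independent NAs and no clustering term.

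The steps below do not need the rate. They take the plan's 80% at 115 as exact for independent NAs. Writing B = 1/μ₀ + 1/μ₁ + 2k, with μ₀ and μ₁ the mean counts and k the dispersion,

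B = 115 × (0.4055)² / (2.802)² = 115 × 0.1644 / 7.849 = 2.41.

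**2. The dropout step.** 115/150 = 76.7%, so the increase covers a loss of 23.3%. If that loss occurs, nothing is left for clustering.

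**3. Adding the units.** With m evaluable NAs per unit, DE = 1 + (m − 1) × ICC, and

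power = Φ( ln 1.5 / √(B × DE / 115) − 1.960 ).

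With few units, a noncentral t with (total units − 2) degrees of freedom is more realistic.

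Worked case: 10 units per arm, 15 recruited and 11.5 evaluable per unit, ICC 0.05.

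- DE = 1 + 10.5 × 0.05 = 1.525
- Effective n = 115 / 1.525 = 75 per arm
- Standard error of the log ratio = √(2.41 × 1.525 / 115) = 0.179
- Power = Φ(0.4055/0.179 − 1.960) = Φ(0.31) = 62%, or 57% with t on 18 degrees of freedom
- Detectable ratio at 80% power = exp(2.802 × 0.179) = 1.65

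**4. Range at 115 evaluable per arm.**

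| Units per arm | Evaluable per unit | ICC | DE | Power (normal) | Power (t) |
|---|---|---|---|---|---|
| 23 | 5 | 0.01 | 1.04 | 78% | 77% |
| 15 | 7.7 | 0.01 | 1.07 | 77% | 74% |
| 15 | 7.7 | 0.02 | 1.13 | 75% | 72% |
| 10 | 11.5 | 0.05 | 1.53 | 62% | 57% |
| 6 | 19.2 | 0.10 | 2.82 | 39% | 33% |

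**5. If nobody drops out.** With 150 per arm in 10 units of 15 and ICC 0.05, DE = 1.70 and power is 69% (64% with t). By the normal approximation, 150 per arm holds 80% only while DE stays at or below 150/115 = 1.30.

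**The case against.** The best counter-argument is that the independence of NAs is inferred. This is a journal article, its power paragraph is condensed (it omits the baseline rate as well), and a clustering term could already sit inside the 115. The numbers allow it: a control rate of 1.0 needs 80 per group for independent NAs, and 115/80 = 1.44, close to the design effect of 1.45 for 10 NAs per unit at ICC 0.05. This cannot be strictly excluded. Nothing in the text supports it, however: the listed inputs contain no clustering term and the only inflation described is for dropout.

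Other points stand in part.

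- **Size of the loss.** It rests on assumed inputs, and with small units and an ICC near 0.01 it is slight (about 77% to 78% by the normal approximation). The direction does not depend on those inputs.
- **Baseline recordings.** Adjusting for them could recover some precision. The article claims no such gain, and its size for sparse counts is unknown.
- **Group supervision.** It can add correlation only in the intervention arm, since controls receive the education after data collection. Managers, colleagues, routines and clients are shared within units in both arms.
- **The clustering remark in the analysis section.** It shows that dependence was expected. It concerns the analysis and does not bear on the sample size.
- **Validity.** Neglecting clustering at the planning stage costs power; it does not by itself bias the estimate or inflate the Type I error.

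**Conclusion.** The concern holds. As written, 115 NAs per group for 80% power at a rate ratio of 1.5 is a statement about independent NAs, and the design allocates units. For any positive ICC, power at 115 evaluable per group is below 80%.

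How far below cannot be fixed from the article. In the central case power is 62% by the normal approximation and 57% with t. The range shown runs from 78% down to 33%. These figures assume equal unit sizes, 115 evaluable of 150 recruited, the plan's 80% taken as exact without clustering, and no gain from baseline adjustment.

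This must be corrected because it is an affirmative claim about the primary comparison that the stated allocation does not support, and is more than an omitted detail.

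**What to change.** Rewrite the power paragraph in Settings and samples for allocation by unit.

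- State the expected number of units per arm, the NAs per unit and an ICC range, for example 0.02 to 0.10, together with the control rate and dispersion behind the 115.
- Apply 1 + (m − 1) × ICC, and use a t reference with (total units − 2) degrees of freedom.
- Keep the 300 NAs, but replace the claim of 80% power at a rate ratio of 1.5 with the power, or the detectable rate ratio, that 300 NAs in the planned units give after the expected dropout. Remove the statement that 115 per group suffices.
- Reconcile the sentence about randomly assigning participants with the alternate allocation of units, and name the home care unit as a level of clustering in the primary analysis.

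The cost is wording and a short recalculation. The reported power will be less favourable. No additional participants are needed.

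### The article says participants are randomly assigned, but the procedure it describes is alternation of home care units, in a prospective controlled study labelled case–control

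*Protocol article*

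**What the plan says.** The protocol article describes the allocation and the design in four ways.

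- **Unit and method, first statement** (Settings and samples): "Participants will be randomly assigned to either control" or intervention, 150 in each group.
- **Unit and method, second statement** (same section): "The randomisation is done by recruiting every second unit to the intervention versus the control group". The reason given is "to aim for an even distribution of the number of units in each group".
- **Design label**: the Design section says the programme is "designed as a multicentre case–control study with a pre-post, intervention design", and the abstract says "A multicentre case–control study with pre- and post-assessments was designed".
- **Reporting standard** (Design): "the STROBE guidelines for the conduct and dissemination of observational studies will be used".

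Settings and samples also describes entry to the study. Units come in through managers willing to implement the programme. A project researcher visits and informs the NAs. Then: "Every NA, at each home care unit, will be offered to participate in the ACTION programme. After informed consent, they will be included". The units are said to be unaware of which group they will join. Recruitment runs in two stages, one per university, each aiming for 75 NAs per group.

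**The concern.** Two things are wrong as written.

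First, the unit and the method of allocation are misdescribed. Taking every second unit is a fixed rule: a unit's arm follows from its place in the recruitment order. All consenting NAs in a unit share that arm, so no NA is individually assigned. A reader who stops at the first statement will believe the groups were formed by individual randomisation, and will give the comparison a protection it does not have.

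Second, the design label does not fit. A case–control study selects people by outcome and looks back at exposure. Here the investigators assign an intervention, collect data before and after it, and compare with a group followed over the same period.

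What is at stake is the basis for a causal reading of the group difference. If whoever lines up the next unit knows its arm, the choice or order of units can follow that knowledge. Units with more motivated staff or more supportive managers could then collect in one arm, and the difference could look like an effect of the programme.

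**Working it through.** No figure in the article bears on this point, so the check is a comparison of texts plus a calculation of predictability.

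**Texts side by side**

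| Feature | What the article claims | What the described procedure does |
|---|---|---|
| Unit allocated | Participants | Home care units |
| Method | Random | Every second unit, no chance element |
| Design | Case–control, STROBE | Prospective, investigator-assigned, concurrent control, pre and post measures |
| Who is unaware of the arm | The units | Nothing is said about the recruiting researchers |

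**Predictability of the next arm**

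Inputs: the alternation rule (Settings and samples), and an assumed number of units *n*, because the article gives none. The starting arm is assumed to be chosen at random, which favours the plan since the article does not say so. The guesser is assumed to know the past allocations.

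- *Alternation.* The first arm is guessed with probability 0.5 and each of the other *n* − 1 with certainty. The expected share guessed correctly is (0.5 + *n* − 1)/*n* = (*n* − 0.5)/*n*.
  - *n* = 10: 9.5/10 = 95.0%
  - *n* = 20: 19.5/20 = 97.5% (a simulation gives 97.5%)
  - *n* = 40: 39.5/40 = 98.75%
- *Simple randomisation.* 50% for any *n*.
- *Random permuted blocks of 4 or 6.* The best strategy is to guess the arm that is behind so far. In a complete block of size 2*b* it gets *b* + 2^(2*b* − 1)/C(2*b*, *b*) − 0.5 right on average.
  - Block of 4: 2 + 8/6 − 0.5 = 2.83 of 4, or 70.8%
  - Block of 6: 3 + 32/20 − 0.5 = 4.10 of 6, or 68.3%
  - Simulation with the two sizes mixed at random over 20 units, the last block cut off where needed: 68.5%

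So alternation is almost wholly predictable whatever the number of units. Blocking keeps the even split the authors want and is much less predictable, but it does not reach 50% for someone who tracks past allocations. For that reason the timing of release matters as well as the random list.

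**The case against.** The strongest reply is that the article has safeguards and that the fault is mainly one of naming. Much of this is fair.

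- **Units are unaware of their arm.** This may limit self-selection by managers and NAs, provided it holds until consent. It stands as a mitigating feature. It does not hide the next arm from the researchers who recruit.
- **Consent seems to come before the arm is known.** A reader might infer that NAs consent knowing their group. The order of the text (information, consent, inclusion, units unaware of their arm) leans the other way, though no explicit timing rule is given. Offering participation to every NA in a unit also limits selection of individuals by researchers.
- **Who does what is not stated.** A reader might infer that the same people contact managers, take consent and apply the sequence. The article says only that a project researcher visits and informs. It does not say who performs the other steps.
- **Baseline is measured.** Under Analyses and data processing, pre and post counts are compared between groups. A reader might assume a baseline imbalance and convert it into a false effect using post-intervention data alone, but that is not the planned comparison. Baseline recordings allow adjustment for measured imbalance. They do not deal with unmeasured differences such as motivation.
- **One procedure, badly named.** The second allocation statement can be read as explaining the first, and the pre-post controlled structure is clear from the rest of the text. The case–control label is therefore an error of terminology more than of analysis. But the article still claims random assignment, and no reading of the described procedure supplies it.

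**Conclusion.** The point holds. The article claims random assignment of participants and describes deterministic alternation of units. The case–control label and the choice of STROBE do not match a prospective, investigator-assigned, concurrently controlled intervention study. These are errors in the stated text and do not depend on detail left to another document.

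On size, after the first unit every later arm is predictable to anyone who knows the previous one. That is 97.5% overall with 20 units (95.0% with 10, 98.75% with 40), given a random start and knowledge of past allocations; the numbers of units are assumptions. The appropriate comparator for a scheme that keeps the numbers even is about 68.5%, not 50%.

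The consequence is a risk confined mainly to the choice and order of units by recruiters who know the next arm. The documents do not show that bias occurs, and they give no basis for putting a figure on it.

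**What to change.** **For units not yet allocated**

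1. Replace alternation with a computer-generated random sequence of home care units, stratified by university site and blocked to keep the numbers of units even.
2. Have it held by someone not involved in recruitment, and released for a unit only after its NAs have consented and preferably completed the baseline recording and questionnaire.
3. State that units, not participants, are randomised. Call the study a cluster-randomised controlled trial and report it by the CONSORT cluster extension in place of STROBE.

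**For units already alternated**

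Drop both the random-assignment and the randomisation wording. Describe the study as a non-randomised cluster-controlled pre-post study, and say whether the recruiting researchers knew the next arm.

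**In either case**

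Remove the case–control label from the abstract and the Design section.

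**Cost**

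Wording changes and a short random list. For units still to be allocated, the arm is disclosed slightly later, and holding it back until baseline is complete brings some minor logistics at each unit. The authors' aim of an even split is kept by the blocking.
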